## Methods

### Study Design and Population

This is a prospective, multicenter, observational cohort study for the early detection of pancreatic cancer in Japanese patients. The study was initiated in September 2020 and aims to recruit at least 150 patients. The aim of the study is to assess whether using a scoring metric to screen for known pancreatic cancer risk factors will improve the rate of early identification in this patient population. The flowchart of patient enrolment and evaluation is summarized in Figure 1. The study is registered in UMIN-CTR Clinical Trials Registry (UMIN000041624). Patients who seek consultation at one of five participating local clinics in the Tsu City area until September 30, 2022, will be referred through the regional medical reference system to the Faculty of Medicine, Gastroenterology, and Hepatology at Mie University Graduate School for a detailed examination for pancreatic cancer. 

Prespecified risk factors and associated point scores will be assessed as follows: symptoms (abdominal pain, jaundice, back pain, or weight loss): 1 point; newly diagnosed diabetes mellitus (type 2) or worsening of diabetes: 1 point; family history of pancreatic cancer (parent, child, or siblings, including other types of pancreatic neoplasms): 1 point; abnormal serum amylase level (under 44 U/mL or over 132 U/mL): 1 point; elevated serum CA19-9 level (>37 U/mL [15]): 1 point; pancreatic duct dilation (>3 mm) or pancreatic cyst detected by abdominal ultrasound: 2 points [11]. Adults aged 20 years or older scoring ≥2 points on this metric for prespecified pancreatic cancer risk factors will be eligible for inclusion (those scoring 2 or less but at high risk for pancreatic cancer will be referred for follow-up, but not included in the study). The total number of patients diagnosed with pancreatic cancer and the subsets of patients with surgically resectable pancreatic cancer and Stage 0/I pancreatic cancer will be determined (Figure 1). After registration, participants will undergo hospital visits every 6 months for a period of 2 years.

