### Sample Size

We based our sample size on data from a previous study, in which 28 patients were diagnosed with pancreatic cancer among 224 subjects who had 2 or more pancreatic cancer risks [14]. The risks prespecified in this study are considered equivalent to those reported previously, meaning that the rate of the patients diagnosed with pancreatic cancer is expected to be approximately 10%. To obtain estimation accuracy (95% CI) of ±5%, the required number of subjects is calculated as 138. The planned number of participants in this study is 150. We expect that approximately 100-150 patients with ≥2 points on the pancreatic cancer risk scoring metric will visit the participating clinics per year and that 80% of these eligible patients will give consent to participate in the study [14]. Therefore, in the 2-year referral period, 160-240 participants are expected to enroll in this study. However, when the number of patients reaches 150, registration will continue because this a prospective observational study without any intervention.

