### Statistical Analyses

Patient characteristics will be summarized using descriptive statistics with frequency, mean, and standard deviation. The following items will be evaluated: sex, age, symptoms suggestive of pancreatic cancer (abdominal pain, jaundice, back pain, and weight loss), newly diagnosed or worsening of type 2 diabetes, family history of pancreatic cancer, abnormal laboratory test value for serum amylase (high or low) or serum CA19-9 (high), pancreatic duct dilation, or pancreatic cyst detected by echography. Participants’ BMI and smoking status will also be recorded for use in adjusted analyses.

Loss of participants to follow-up will be minimized by monitoring missed appointments and contacting participants promptly. Where key data items are unavailable or only partially reported, we will use multiple imputation to impute missing data where indicated.

Data on patients with a confirmed diagnosis will be summarized using descriptive statistics according to resectability classification [16]. Binomial logistic regression analysis (both univariate and multivariate analyses) will be performed with a diagnosis of pancreatic cancer as the objective variable and each risk factor and the result of an imaging test as explanatory variables. For the primary multivariable analysis, variables will be selected with a two-sided significance level of 5%. In addition to the unadjusted analyses, logistic regression analyses adjusted for BMI and smoking status will be conducted.

Sensitivity analysis will be conducted to generate multivariable prediction scores based on all available risk factors, regardless of performance or significance on univariable analysis, and based on alternate combinations of risk factors as indicated. Formal comparisons of the relative goodness-of-fit of each model will be conducted through derivation of the Akaike Information Criteria and/or the Bayesian Information Criteria as indicated. We will compare the performance of the prediction score based on this primary model against those of the sensitivity analysis models.

No interim analysis or subgroup analysis will be performed. A separate follow-up study will be conducted to evaluate the 5-year survival rate of pancreatic cancer in the region. SPSS statistical software (Version 25.0, IBM Corp) will be used for all analyses.

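### Choosing variables for the primary multivariable model at p<0.05, with about 15–30 expected cancers in a cohort restricted to scores of 2 or more, makes selection unstable and lets entry-rule bias in; the all-item model should be primary

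*Protocol article*

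**What the plan says.** The Statistical Analyses section plans univariate and multivariate logistic regression of a pancreatic cancer diagnosis on each risk factor and an imaging result. For the lead model it fixes a rule: "For the primary multivariable analysis, variables will be selected with a two-sided significance level of 5" per cent. The selection algorithm is not named. The sensitivity analysis builds scores from all available risk factors "regardless of performance or significance on univariable analysis", which suggests that the primary rule is a univariable screen. The selected model is then used as a score: "We will compare the performance of the prediction score based on this primary model against those of the sensitivity analysis models". AIC and/or BIC will compare fit. Analyses adjusted for BMI and smoking are additional.

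Two other sections bear on this rule:

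- Study Design and Population restricts entry on the same items: "Adults aged 20 years or older scoring ≥2 points on this metric". The ultrasound finding (duct dilation or cyst) scores 2 points and qualifies a patient alone. Every other item scores 1.
- Sample Size is set for the precision of the diagnosis rate, not for a model: "To obtain estimation accuracy (95% CI) of ±5%, the required number of subjects is calculated as 138", and "The planned number of participants in this study is 150".

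**The concern.** Two features of the design work against the 5% rule.

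**Few events.** With a handful of cancers per candidate, a p-value threshold mostly misses real predictors. Those that pass tend to do so because their estimates happened to be large.

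**Entry depends on the predictors.** A participant without the ultrasound finding must have at least two other items, while one with it may have none. Within the cohort, ultrasound-negative patients therefore carry more of the other risk factors. A one-variable comparison sets the ultrasound finding against that enriched group and understates its effect. The 1-point items are understated for a similar reason.

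At stake is the only analysis described that examines how the items of the score relate to cancer. Evaluating that score is the study's stated objective.

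**Working it through.** **1. The plan's own figure.** n = 1.96² × p(1−p)/d², with p = 0.10 and d = 0.05, gives 3.8416 × 0.09/0.0025 = 138.3. The stated 138 reproduces. It is a precision calculation for one proportion.

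**2. Expected cancers.** The article says "the rate of the patients diagnosed with pancreatic cancer is expected to be approximately 10" per cent. Its source is a study in which "28 patients were diagnosed with pancreatic cancer among 224 subjects who had 2 or more pancreatic cancer risks", and 28/224 = 12.5%. Expected enrolment is 100–150 eligible patients a year × 2 years × 80% = 160–240. Candidates: six items + one imaging result = 7 at least.

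| Participants | Rate | Cancers | Cancers per candidate |
|---|---|---|---|
| 150 | 10% | 15 | 2.1 |
| 150 | 12.5% | 18.75 | 2.7 |
| 160 | 10% | 16 | 2.3 |
| 240 | 10% | 24 | 3.4 |
| 240 | 12.5% | 30 | 4.3 |

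**3. Effect of the entry rule on univariable odds ratios.** The article gives no item prevalences or true odds ratios, so these are assumed. Let items be independent in the source population with prevalence p_j, and logit P(cancer | x) = α + Σβ_j x_j. Enumerate the 64 item patterns, keep those scoring at least 2, set α so that 10% have cancer, and compare the odds of cancer with and without each item.

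With prevalences 30/12/6/15/10/20% (symptoms, diabetes, family history, amylase, CA19-9, ultrasound), ultrasound-positive participants carry on average 0.30 + 0.12 + 0.06 + 0.15 + 0.10 = 0.73 other items. Ultrasound-negative participants carry at least 2.

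- All true odds ratios 2.5: ultrasound appears as 0.80, the other items as 1.64–1.83.
- True ultrasound odds ratio 4, 6 or 6.25, others 2.5: it appears as about 1.3, 1.9 and 1.9.
- Over other prevalence sets, 2.5 appears as about 0.8–1.2 and 6.25 as about 1.9–3.0. With much commoner items (ultrasound 50%, symptoms 60%), 2.5 appears as 1.35.

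**4. The full model is not biased.** Entry depends only on x, so P(cancer | x, score ≥ 2) = P(cancer | x). In a large simulated cohort (prevalences 35/20/8/20/15/25%, all true odds ratios 2), the six-item model returned 1.98–2.03. The univariable odds ratios were 1.46–1.55 for the 1-point items and 0.93 for ultrasound.

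**5. Effect of 5% selection.** Six items simulated, without the imaging result.

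*Prevalences as in step 3, odds ratios 2.5, univariable screen.* At 150 participants and 10%, nothing was selected in 44% of studies, and on average 0.8 of 6 items were. At 240 and 12.5%, nothing was selected in about 24%. Across 150–240 participants and rates of 10–12.5%, AUC in new patients was 0.54–0.57 for the selected model and 0.62–0.66 for a forced six-item Firth model.

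*Prevalences as in step 4, 10% rate, unpenalised models:*

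| True OR | N | Method | Nothing selected | AUC of selected model, apparent → new patients | AUC of full model, new patients |
|---|---|---|---|---|---|
| 2 | 150 | backward | 54% | 0.69 → 0.55 | 0.58 |
| 2 | 150 | univariable | 58% | 0.68 → 0.55 | 0.58 |
| 2 | 240 | backward | 40% | 0.67 → 0.56 | 0.59 |
| 3 | 150 | univariable | 36% | 0.69 → 0.58 | 0.67 |
| 3 | 240 | backward | 13% | 0.72 → 0.62 | 0.69 |

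At odds ratio 2 and N = 150 under backward elimination, items that survived had median odds ratios of 3.9–5.4 against a true 2.0.

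**The case against.** Several points on the other side stand:

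- **The primary endpoint is untouched.** It is the diagnosis rate with its 95% CI. Regression is neither a primary nor a listed secondary endpoint. The Discussion calls this an initial study and leaves the value of each item for early-stage detection to a larger one.
- **Fifteen cancers is the low end.** Registration continues past 150, and the cited rate is 12.5%.
- **BMI and smoking are not candidates for selection.** They belong to separate adjusted analyses, so the count is about seven, not nine.
- **Univariable screening is inferred.** Backward elimination, however, also gave unstable selection and poorer discrimination.
- **An all-factor model is already planned**, with AIC/BIC. It is subordinate to the selected model, though.
- **Forcing items in does not itself remove optimism.** At 150 participants and odds ratios of 2.5, the drop in AUC is 0.680 − 0.562 = 0.118 for the selected model and 0.739 − 0.622 = 0.117 for the Firth model. The gain is in discrimination in new patients.

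Four stronger readings are tempting but not supported:

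- *The ultrasound item will look protective.* Reversal arises when it has the same true odds ratio as a 1-point item and the items are not common. If double points mean double log-odds (2.5² = 6.25), it is attenuated to about 1.9, not reversed.
- *Every odds ratio in the regression is biased by the entry rule.* Step 4 shows that a correctly specified all-item model is not.
- *Items will be removed from the referral metric.* The article does not say so.
- *Performance will be reported without correction.* The article is silent, and a condensed article may leave that detail to the full protocol.

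**Conclusion.** The concern holds in a limited form. The article fixes a 5% selection rule for its lead multivariable model and uses the result as a prediction score. With 2.1–4.3 cancers per candidate, that rule is unstable: nothing was selected in roughly a quarter to a half of simulated studies, with extremes of 13% (odds ratios of 3, 240 participants) and 58% (odds ratios of 2, 150 participants). By dropping score items it admits an entry-rule bias that the all-item model avoids. It also cost about 0.03–0.09 of AUC in new patients in the unpenalised comparisons tabulated.

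The event counts come from the article. The prevalences, true odds ratios and independence of items are assumptions, and the imaging result is not simulated, so the AUCs show direction and rough size and do not forecast the planned model. Attenuation of the ultrasound odds ratio and lower discrimination after selection appeared in every setting tried. The change is worth making, but it does not threaten the primary result.

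**What to change.** In the Statistical Analyses section:

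1. Remove the 5% selection rule. Make the all-item model, now only a sensitivity analysis, the primary multivariable model, with the six prespecified score items forced in and fitted by Firth or ridge logistic regression.
2. Report univariable odds ratios as descriptive only, with a note that entry at 2 or more points attenuates them, usually most for the ultrasound item.
3. Compare models on bootstrap optimism-corrected AUC and calibration, repeating any selection step within each resample.
4. Label the model exploratory and applicable only to patients scoring at least 2. Penalisation stabilises the estimates but does not supply the missing events.

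No extra patients or data are needed. The cost is plan wording, some code outside the standard SPSS menus, and less striking odds ratios and performance figures.

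### The adjusted logistic regression names BMI and smoking status but not age, so item odds ratios may stay confounded by age and the score comparison cannot show what the items add beyond it

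*Protocol article*

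**What the plan says.** All of this is in the Methods of the protocol article.

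- **Adjustment set** (Statistical Analyses): "BMI and smoking status will also be recorded for use in adjusted analyses", and, in addition to the unadjusted analyses, "logistic regression analyses adjusted for BMI and smoking status will be conducted". No other adjustment variable is named.
- **Age and sex** (Statistical Analyses): they appear in the paragraph on descriptive summary of patient characteristics, which reads "The following items will be evaluated: sex, age, symptoms suggestive of pancreatic cancer" and continues through the scored items.
- **Explanatory variables** (Statistical Analyses): the regression takes "each risk factor and the result of an imaging test as explanatory variables".
- **Risk factors** (Study Design and Population): under "Prespecified risk factors and associated point scores will be assessed as follows" there are six items: symptoms, new or worsening diabetes, family history, abnormal amylase, raised CA19-9, and duct dilation or cyst on ultrasound. Neither age nor sex is scored.
- **Entry** (Study Design and Population): "Adults aged 20 years or older scoring ≥2 points on this metric" are eligible. No upper age limit is stated.
- **Selection and sensitivity models** (Statistical Analyses): for the primary multivariable model, "variables will be selected with a two-sided significance level of 5" percent. Sensitivity models use every available risk factor or other combinations of them, and models are compared by AIC and/or BIC.

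The article gives no reason for adjusting for BMI and smoking but not for age.

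**The concern.** The article states a specific adjustment set, so this is not a detail simply left to a fuller document. Design does not narrow the age range beyond the lower limit of 20, and the score has no age item. Age could plausibly be related to some items and also to the diagnosis. Where both relations hold, an item's odds ratio takes up part of the age effect, and BMI and smoking will not in general remove it.

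Two results are at stake. The first is the adjusted odds ratio of each item, which a reader may take as its own contribution. The second is the comparison of prediction scores: if every candidate model is built from the risk items and imaging alone, AIC and BIC rank those models against each other but cannot say whether the items improve on age.

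**Working it through.** **1. The plan's own figure.** Sample Size gives an expected diagnosis rate p = 0.10 and a 95% CI half-width d = 0.05.

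n = 1.96² × p(1 − p) / d² = 3.8415 × 0.09 / 0.0025 = 138.29

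The stated 138 reproduces. It rests on a single proportion and does not depend on the regression, so nothing below changes it.

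**2. Can age enter by another route?** The explanatory variables are the risk factors and the imaging result. The risk factors as defined in Study Design and Population exclude age and sex. The adjustment set is BMI and smoking. The sensitivity models are again described in terms of risk factors. On the defined terms, no model contains age.

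**3. Possible size of bias.** The documents give no age distribution and no age associations, so all inputs here are assumptions: age mean 65 and SD 12 (limited to 20–95), item prevalence about 30%, diagnosis rate 10%, true item odds ratio 1.0, smoking prevalence 25% with odds ratio 1.5 for the diagnosis, BMI unrelated to it, and both BMI and smoking unrelated to age. A simulation of 400,000 subjects gives the large-sample item odds ratio:

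| Age OR per decade with diagnosis | Age OR per decade with item | Item OR, BMI and smoking only | Item OR, age added |
|---|---|---|---|
| 1.0 | 2.0 | 0.99 | 0.99 |
| 2.0 | 1.0 | 1.00 | 1.00 |
| 1.3 | 1.3 | 1.10 | 1.00 |
| 1.6 | 1.6 | 1.33 | 1.00 |
| 2.0 | 2.0 | 1.76 | 1.01 |

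Over all 16 combinations of 1.0, 1.3, 1.6 and 2.0, the item odds ratio with age added lies between 0.97 and 1.02. Without age it lies between 0.99 and 1.02 whenever either association is null.

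A hand approximation agrees in order of size. The inflation factor is exp(log OR per SD of age × age difference in SD). With an odds ratio of 1.5 per SD and a difference of 0.3 SD it is exp(0.405 × 0.3) = 1.13. With 2.0 and 0.5 SD it is exp(0.693 × 0.5) = 1.41.

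**4. Room in the model.** Expected events at 10% are 150 × 0.10 = 15 at the planned size and 240 × 0.10 = 24 at the top of the expected enrolment. Counting one term each for six risk factors, the imaging result, BMI and smoking gives 9 terms.

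| Model | Terms | Events per term, N = 150 | Events per term, N = 240 |
|---|---|---|---|
| As planned | 9 | 15/9 = 1.67 | 24/9 = 2.67 |
| Plus age | 10 | 15/10 = 1.50 | 24/10 = 2.40 |
| Plus age and sex | 11 | 15/11 = 1.36 | 24/11 = 2.18 |

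The full model is overloaded before anything is added, so each added term has to be worth its place.

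**The case against.** **The aim is prediction, not causation.** The study evaluates a score for detection. An item that marks older age and so finds cancer is truly predictive. This is a fair reason not to judge the plan by a causal standard, and the article nowhere says that its adjusted analysis controls confounding. It does not remove the point: for a score, too, it matters whether the items add to age, which costs nothing to ascertain.

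**Age may already be covered.** Age and sex stand in the same list as items that do become explanatory variables, so a lenient reader could count them as risk factors. The definition in Study Design and Population speaks against this. Even on that reading, selection at the 5% level with about 15 events would not guarantee that age is kept.

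**The noise is larger than the bias.** With 30% item prevalence, a true odds ratio of 1 and 15 events in 150, the expected cells are 4.5, 40.5, 10.5 and 94.5. Then SE = √(1/4.5 + 1/40.5 + 1/10.5 + 1/94.5) = 0.594, and the univariate 95% CI spans a factor of exp(1.96 × 0.594) = 3.2 either way. At N = 240 the factor is about 2.5. This stands: one estimate could not reveal a bias of 1.1 to 1.8. It limits how much rests on these odds ratios, but it is no reason to leave out a collected variable.

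**The analysis is peripheral.** This also stands. The primary endpoint is a diagnosis rate and no secondary endpoint is an odds ratio. The Discussion leaves the value of each item for early-stage detection to a larger future study.

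**Conclusion.** The point holds in conditional form. As written, the plan yields adjusted odds ratios and prediction scores that leave out age in a cohort open from age 20. If age is related to both an item and the diagnosis, that item's odds ratio may stay confounded. Under assumed age odds ratios of 1.3 to 2.0 per decade with both, a null item would show about 1.1 to 1.8. With either association null there is no bias. The simulation leaves the other score items out of the model; they could absorb part of the age effect.

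A reader might infer more than the documents support:

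- **That every item's odds ratio is biased.** The documents give no age association for any item. The case is plausible for diabetes, cyst and duct dilation, and bias may differ from item to item.
- **That the bias rivals the effect the study is designed to detect.** No target odds ratio is stated; the study is sized on the precision of a proportion.
- **That the main results are at risk.** The primary and secondary diagnosis-rate endpoints do not depend on the regression.

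The change is worth making before the final analysis because the variable is already in hand.

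**What to change.** - Force age, continuous and as one linear term, into the adjusted logistic model, exempt from the 5% selection.
- Include age in the same way in at least one of the prediction models compared by AIC or BIC, so that the comparison shows what the items add beyond it.
- Add sex only if the event count allows. With about 15 to 24 expected events, penalised estimation (for example Firth) is preferable. The plan states that SPSS will be used for all analyses, so either confirm that the penalised method can be run there or amend that sentence.
- Keep the model adjusted for BMI and smoking only as a secondary result.
- State whether age and sex count as risk factors in the regression, to remove the ambiguity in the list of items.

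The cost is slightly wider intervals. Age takes events per term from 1.67 to 1.50 at N = 150. No new data are needed, and the sample size and endpoints do not change.

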**Objective:**

The aim of this prospective, observational trial is to evaluate a scoring metric for systematic early detection of pancreatic cancer in Mie Prefecture, Japan.

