### Study Endpoints

The primary endpoint is the diagnosis rate (number of patients diagnosed/total number of study participants) for pancreatic cancer, calculated with a 95% CI. The secondary endpoints include the diagnosis rates of pancreatic cancer by stage, pancreatic neoplasms other than pancreatic ductal adenocarcinoma, Stage 0/I pancreatic cancer at each visit, and surgical resection. For patients with a definite diagnosis of pancreatic cancer, a frequency table will be created based on the resectability classification [16].

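### Beyond the ≥2-point entry rule, no described analysis uses the prespecified total score, and the score comparison covers only scores newly fitted to the study data

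*Protocol article*

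**What the plan says.** The Objective gives the purpose as "to evaluate a scoring metric for systematic early detection of pancreatic cancer in Mie Prefecture, Japan". Study Design and Population words it as a wish to "assess whether using a scoring metric to screen for known pancreatic cancer risk factors will improve the rate of early identification". That section also fixes the metric: five items worth 1 point each, and one (duct dilation or cyst on ultrasound) worth 2.

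The points total is used in one place, the entry rule: "Adults aged 20 years or older scoring ≥2 points on this metric for prespecified pancreatic cancer risk factors will be eligible for inclusion". Study Endpoints then states: "The primary endpoint is the diagnosis rate (number of patients diagnosed/total number of study participants) for pancreatic cancer, calculated with a 95% CI". Every participant has passed the cutoff, so this rate is the yield of the cutoff.

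Statistical Analyses describes logistic regressions whose explanatory variables are the separate risk factors and an imaging result, with variables selected at the two-sided 5% level. Sensitivity analyses will "generate multivariable prediction scores based on all available risk factors" and on other combinations of factors. Models are ranked by AIC and/or BIC. The performance comparison is stated in full as: "We will compare the performance of the prediction score based on this primary model against those of the sensitivity analysis models".

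**The concern.** The scale under evaluation has fixed weights and needs no fitting, yet it is neither a predictor nor a comparator in the modelling. Two questions that belong to the stated aim are left open. Does the chance of cancer rise from 2 points to 3 to 4 and above? Do the assigned weights, including the double weight for the ultrasound finding, discriminate as well as weights estimated from the data?

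The scores that are compared are estimated from few diagnoses. Their performance in the data that produced them will be flattering, and the plan names no fixed benchmark to set beside them. A report could put forward a re-derived score without ever showing how the original did in the same patients.

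**Working it through.** **1. The plan's own figure.** Inputs from Sample Size: expected rate 10%, half-width 5 points. n = 1.96² × 0.10 × 0.90 / 0.05² = 138.3. The stated 138 is reproduced.

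**2. Expected diagnoses.** Sample Size gives a working rate of 10%, a source rate of 28/224 = 12.5%, a planned size of 150, projected enrolment of 160-240, and registration continuing past 150.

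| Participants | at 10% | at 12.5% |
|---|---|---|
| 150 | 15 | 18.75 |
| 160 | 16 | 20 |
| 240 | 24 | 30 |

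**3. Events per variable.** With the six scored items as the candidate terms: 15/6 = 2.5 to 18.75/6 = 3.1 at 150 participants, and 24/6 = 4.0 to 30/6 = 5.0 at 240. With one imaging term added (seven terms): 15/7 = 2.1 to 30/7 = 4.3 over the same range. The fixed total needs one coefficient, so all 15-30 events support it.

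**4. Where the total score appears.** Its range is 0 to 1+1+1+1+1+2 = 7, hence 2 to 7 among participants.

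| Element of the plan | Uses the points total? |
|---|---|
| Eligibility | Yes, as ≥2 |
| Primary and secondary endpoints | Only through eligibility |
| Univariate and multivariate regressions | No, separate items |
| Sensitivity-analysis scores | No, refitted |
| AIC/BIC and performance comparison | No, fitted models only |

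**5. How optimistic a refitted score would look.** This is an illustrative simulation. Its item prevalences and odds ratios are assumptions, not document figures. Prevalences are 0.4 symptoms, 0.3 diabetes, 0.1 family history, 0.3 amylase, 0.3 CA19-9 and 0.5 duct/cyst. Items are independent, participants are restricted to ≥2 points, and a six-item logistic model is refitted without selection in 300-400 simulated studies per row. Repeat runs agree to about 0.01.

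| Assumed item effects | N, rate | Refit, in sample | Refit, new patients | Fixed total |
|---|---|---|---|---|
| None | 150, 10% | 0.68 | 0.50 | 0.50 |
| None | 240, 12.5% | 0.63 | 0.50 | 0.50 |
| OR 1.5 per point | 150, 10% | 0.71 | 0.56 | 0.61 |
| OR 1.5 per point | 240, 12.5% | 0.67 | 0.57 | 0.61 |
| OR 2 for every item | 150, 10% | 0.75 | 0.62 | 0.66 |
| CA19-9 OR 6, symptoms OR 4, others 1 | 150, 10% | 0.82 | 0.73 | 0.59 |
| CA19-9 5, symptoms 3, diabetes 2, duct/cyst 1.5, others 1 | 150, 10% | 0.80 | 0.70 | 0.64 |

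Entries are areas under the ROC curve (AUC). The in-sample figure exceeds the new-patient figure in every row, by 0.09 to 0.18. The ranking of the fixed total against the refit changes with the assumed effects.

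**The case against.** The strongest reply is that the metric is evaluated, as a referral rule. The Introduction frames the hypothesis as one about referral on the metric. The primary endpoint gives the yield at the operating cutoff, the secondary endpoints give it by stage, and the Discussion sets those rates against published data. This stands. A reader might infer that the study will end with nothing to say about its own metric, and the documents do not support that. What is missing is information above the cutoff and a place for the fixed score in the comparison.

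A second reply is that fixed weights are not necessarily better. This also stands. A reader might infer that refitted scores would do worse in new patients than the original points. That holds when item effects are similar or follow the points, and it reverses when a few items dominate. The Discussion itself reports a previous study in which the findings differed in frequency between advanced, early and non-cancer groups, so equal effects cannot be assumed.

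Third, the article does not say that performance will be reported uncorrected, and optimism correction is commonly left to an analysis plan that is not shown here. This is accepted: the lack of a stated validation step is not itself a fault. The omission of the total score is different in kind, because the article specifies the predictors, the selection rule and the comparison set, and the total score is in none of them.

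Finally, the Discussion calls this an initial study, concedes the small sample, and defers the value of each item for early-stage detection to a larger one. That favours a one-coefficient analysis of the total over item-by-item refitting.

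**Conclusion.** The point holds in limited form. The yield of the ≥2-point cutoff will be known. Whether risk rises with points, and whether the assigned weights match refitted ones, cannot be learned from the analyses described.

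The events-per-variable range of 2.5-5 rests on the plan's 10% rate, its 12.5% source rate and 150-240 participants, with six candidate terms; extra terms lower it. Optimism in refitted scores appeared in every scenario tried, and was smaller at 240 participants than at 150. Its exact size depends on the assumed prevalences and effects. AIC and BIC penalise model size, but they do not correct performance reported after selection at 5%. No claim is made about which score is better: that can be judged only if the fixed score is in the comparison.

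The change should be made. The primary endpoint is unaffected.

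**What to change.** In Statistical Analyses:

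1. Add a logistic model with the total score as its single term, and make it the reference in the AIC/BIC and performance comparisons. It is the six-item model with coefficients constrained to the assigned 1:1:1:1:1:2 weights, so the comparison is direct.
2. Tabulate the diagnosis rate by total points (2, 3, ≥4) with exact 95% intervals and, descriptively, the Stage 0/I count at each level. Say that this describes the score and is not a subgroup analysis, since the plan excludes those.
3. State that any AUC is conditional on ≥2 points. Nobody below the cutoff is enrolled, so the cutoff's own sensitivity and specificity cannot be estimated.
4. As a secondary matter, report refitted scores with a bootstrap optimism correction that repeats every selection step.

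The items are already recorded to determine eligibility, so the cost is some added text and computing time. The downside is imprecision. If 150 participants split evenly over the three levels with 10% diagnosed, each level has 5 of 50, and the exact 95% interval is 3.3% to 21.8%. Corrected performance figures will also be lower than uncorrected ones.
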